**Figure 1 figure1:**
[figure not shown]
Study design. EDA: electrodermal activity; HR: heart rate; HRV: heart rate variability; NFC: near-field communication; UMR: University Medical Centre Rostock.

### Apparatus

#### Overview

Stress level was measured both objectively (physiological stress reaction) and subjectively (appraisal of the perceived stress in ecological momentary assessments [EMAs]). Possible stressors were also identified both as subjective perception via questionnaires and objectively by matching physiological stress responses to concurrent ambient conditions, such as noise, interruptions, or specific activities. We compared the objective stress levels to the daily staffing, occupancy level, and other daily changing factors of a hospital ward.

To this end, a combination of wearable and ambient sensors that can measure the physiological (objective) stress reaction as well as possible stressors (causes of stress) is being used. The prototypical setup consisted of a smart wristband, a smartphone, near-field communication (NFC) tags, and Raspberry Pis equipped with microphones to record interruptions (incoming telephone calls) and unexpected tasks (calls from patients). The setup can be seen in Figure 2 and Figure 3. At the end of the study, it will be possible to characterize a normal working day of a palliative caregiver more precisely in terms of physical and psychological stress. The perceived burden will be correlated with bed occupancy and the numbers of patient admissions, discharges, and deaths per day as well as influence of the duty roster design (including the staffing) and frequency of interruptions by telephone or a patient’s bell.

**Figure 2 figure2:**
[figure not shown]
To assess possible stressors, near-field communication (NFC) tags have been programmed and placed in numerous positions on the ward.

**Figure 3 figure3:**
[figure not shown]
Electrodermal activity, heart rate, and skin temperature are recorded with the Empatica E4 research wristband.

#### Body-Worn Equipment

The results of measured electrodermal activity (EDA), HR, and skin temperature should provide information about an SNS reaction to stress [14]. All these parameters are recordable with the Empatica E4 (Empatica Inc) research wristband. Thus, to measure the physiological stress reaction, we used the commercially available Empatica E4 wristband [27]. The E4 wristband possesses a photoplethysmography sensor and 2 electrodes to measure the galvanic skin response at the wrist. It was used to measure pulse, HRV, EDA, and body temperature (surface). The automatic data preprocessing was bypassed, since this would require sending the sensitive data to an alien server. To circumvent these international servers for reasons of data protection, the code of the E4 had been altered, allowing the extraction of raw data. Raw data were then sent to the smartphone, which is also part of the study’s setup, and stored on the phone’s memory until transferred to a local server. The E4 had no display and thus provided no feedback to the participants that could interfere with or distort the measurement. LEDs provided the necessary feedback on the functionality of the wristband, and additional feedback on functionality (and connectivity) was given in the corresponding smartphone app.

In addition to the LED, allowing event marking (ie, a real-time annotation) via tapping the button deposits a record in the session file. The record included the time of the button press (expressed as a Unix time stamp in UTC), which was synchronized with the initial time of the corresponding session. Feedback on the button press was given both visually (illuminating the LED) and audibly (beeping). The button press was used for 2 purposes: (1) logging an event of subjectively perceived stress (a single button press) and (2) logging the event of disinfecting one’s hands (as this can alter the EDA; 2 consecutive button presses).

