The acceleration data were fused to a 3D vector by applying the following equation:

All algorithms for data extraction were written in Python using Jupyter Notebooks and the *Pandas*, *Numpy*, *SciPy*, *Matplotlib*, and *NeuroKit2* libraries.

For stress detection analysis, all stress events marked with a button press will be identified, and windows surrounding this event will be extracted and averaged, leading to one value per stress event per participant. Analogously, the windows surrounding a scan of the NFC tag “relaxation” and the baseline windows will be extracted and averaged as well. Descriptive and inferential statistical analyses will be applied using IBM SPSS Statistics 30. Weighted ANOVAs for correlated samples will be computed to compare the stressful events and the baseline for each physiological parameter.

To examine the predictability of experiencing stress, the subjective ratings given in the EMA will be used as ground truth. Surrounding the EMA, data windows will be extracted from the data for each physiological parameter. A linear regression will be computed with the subjective stress level (EMA) as the dependent variable and entering the means of the physiological variables (HR, HRV, tonic EDA, phasic EDA, temperature, and acceleration) as independent variables. Artificial intelligence approaches will be used to analyze the data where appropriate.

With the data for daily occupancy of patients and the total number of nurses on the same day, we will be able to calculate the relationships of these 2 variables with stress. The minimum occupation level according to the recommendation from the German Society for Palliative Medicine (*Deutsche Gesellschaft für Palliativmedizin*) on staffing in palliative wards [30] of 1.4 nurses per patient will be used as a cutoff to create two subgroups of “well-staffed” and “under-staffed.”

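### Each stress event is marked by a button press that lights up and beeps on the sensor device, so the stress-versus-baseline comparison may partly reflect the marking act

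*Protocol article*

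**What the plan says.** Under Methods, Body-Worn Equipment, the protocol article describes a wristband with a photoplethysmography sensor and two electrodes for skin conductance. Of feedback to the wearer it says: "The E4 had no display and thus provided no feedback to the participants that could interfere with or distort the measurement". The text then notes that LEDs showed whether the device was working. The following paragraph describes event marking with the wristband button: "Feedback on the button press was given both visually (illuminating the LED) and audibly (beeping". The button has two uses: "logging an event of subjectively perceived stress (a single button press" and "logging the event of disinfecting one’s hands (as this can alter the EDA; 2 consecutive button presses". The time of each press is stored.

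Under Data Analyses, the stress-detection analysis is anchored to that press: "all stress events marked with a button press will be identified, and windows surrounding this event will be extracted and averaged". The comparison conditions are handled as follows: "the windows surrounding a scan of the NFC tag “relaxation” and the baseline windows will be extracted and averaged as well". The test is: "Weighted ANOVAs for correlated samples will be computed to compare the stressful events and the baseline for each physiological parameter".

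A separate regression uses windows around the momentary self-ratings, not around presses. Under Strengths and Limitations the article recognises that repeated prompts and the use of technology may themselves add stress and confound the measured response. The button's light and beep are not named there.

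**The concern.** A comparison of two conditions supports a conclusion about stress only if the conditions do not also differ in how they were marked. Here every button-marked stress window contains, by construction, a hand movement to the wristband, pressure on the device that holds the sensors, a light and a beep. Nothing in the text says that baseline windows contain any of these.

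A disturbance locked in time to the press would fall in the stress condition each time. More events or more nurses would not average it out. If it raises phasic skin conductance or acceleration, or disturbs the pulse signal, the ANOVA can show a difference from baseline that is not a stress reaction. This matters because the Introduction makes measuring stress reactions with wearable devices part of the primary goal, and this ANOVA is one of two inferential analyses described for the physiological data.

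**Working it through.** **Step 1: what each window contains, from the text**

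- Stress event: anchored to a single button press (Data Analyses). It contains the press, the light and the beep (Body-Worn Equipment).
- Relaxation: anchored to a phone scan of a tag. No wristband press is needed.
- Baseline: named, but its timing and selection are not described. It is listed apart from the button-marked events. That it contains no press is a likely inference, not a stated fact.
- Self-rating regression: windows around the self-rating, not defined by the button.

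The marking act is therefore tied to the stress condition in the ANOVA and is not built into the regression.

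**Step 2: share of a window that the marking act could occupy**

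The article gives neither a window length nor the duration of any disturbance. Assumed inputs: disturbance r = 5 or 10 s, window w = 30 to 300 s. Share = r / w.

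| Window | r = 5 s | r = 10 s |
|---|---|---|
| 30 s | 5/30 = 17% | 10/30 = 33% |
| 60 s | 5/60 = 8% | 10/60 = 17% |
| 120 s | 5/120 = 4% | 10/120 = 8% |
| 300 s | 5/300 = 2% | 10/300 = 3% |

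This is the share of signal exposed. It is not the bias in the window mean, which also depends on how large the disturbance is. The article gives no figure for that.

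**Step 3: what a systematic shift would do to the test (illustration only)**

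The article has no power calculation to reproduce. Sample and Recruitment gives 12 participants (12/18 = 67%, as stated). Assumptions: one averaged stress-minus-baseline difference per nurse, a paired two-sided 5% test in place of the planned weighted ANOVA, no true stress effect, and a marker shift of d standard deviations of the within-person difference.

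The test statistic then follows a noncentral t with 11 degrees of freedom and noncentrality d × √12. The chance of a significant result is P(|T| > t(0.975; 11)).

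| d | d × √12 | Chance of a significant result |
|---|---|---|
| 0 | 0 | 5% |
| 0.2 | 0.69 | 10% |
| 0.5 | 1.73 | 35% |
| 0.8 | 2.77 | 71% |
| 1.0 | 3.46 | 88% |

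Which row applies cannot be told from the article. The table shows only that a modest systematic shift is enough to mislead, and that a very small one matters little.

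**The case against.** Several points on the other side are sound.

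- **The no-feedback sentence.** It argues from the missing display, so it most naturally means that no measured values were shown. The next sentence openly mentions LED feedback. A reader might infer that the article claims its measurements cannot be distorted and then contradicts itself. The text does not go that far. What stands is that the sentence is worded more broadly than its reason supports.
- **Baseline windows.** A reader might take it as established that they contain no press. The article does not describe them, and such detail may sit in a fuller document.
- **Mechanism.** The wearer triggers the beep deliberately, and the article has no data on any response to it. The windows surround the press, so they may hold signal from before the beep. Interbeat intervals are saved only when signal quality is sufficient, which may limit movement artefact in heart rate and its variability. The article describes no such filter for skin conductance or acceleration.
- **Scope.** The Discussion names feasibility of generating data as the primary outcome, and the self-rating regression does not depend on the button. Reactivity to the assessment is acknowledged in general terms.
- **A ready-made control.** The double press for hand disinfection may look like a negative control. It is not a clean one: it involves two presses and hand movement, and the article itself says disinfection can alter skin conductance.

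These points limit how strongly the concern can be put. None of them separates the marking act from the stress condition in the planned ANOVA.

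**Conclusion.** The point holds as a possible confounder of one analysis. The press, light and beep are built into every button-marked stress window and are not said to be present in baseline, so a difference in the ANOVA cannot be read as a stress reaction without a further check. The size is open. Under the assumed 5 to 10 s disturbance, exposure ranges from 17-33% of a 30 s window to 2-3% of a 300 s window, so the effect could be material or negligible.

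A reader might go further and conclude that the marker is shown to produce the stress reaction, or that all the physiological results are compromised. The article supports neither. It gives no size for any response to the press, and the self-rating regression is not button-anchored. The conclusion rests on one inference (baseline windows without presses) and on assumed durations.

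**What to change.** 1. For the button-marked event analysis, repeat the stress-versus-baseline comparison with a fixed short interval from the press onward masked (for example 10 s), or with pre-press signal only. State the interval before the analysis is run.
2. Claim a detectable stress reaction for a parameter only if the difference persists in that repeat.
3. Select baseline windows that contain no press, and say so.
4. Report masked and unmasked results together.
5. Do not use double presses as a decision rule. They may be shown descriptively.
6. Reword the sentence under Body-Worn Equipment to say that the wristband gave no readout of measured values but did give light and sound on each press.

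The cost is a script change and some wording. Press times are already stored, so no new data are needed, and the article still describes this analysis as to be done. The downside is the loss of some genuine signal just after the press. If windows were symmetric about the press (an assumption), a 10 s mask would remove 10/15 = 67% of the post-press half of a 30 s window but 10/150 = 7% of that half in a 300 s window. This is why both results should be shown. Neither variant removes the movement of reaching for the button just before the press, so acceleration results need particular caution.

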#### Preparation of the Hospital Ward

To assess possible stressors, NFC tags (Figure 2C) had been programmed and placed in numerous positions on the ward. The NFC tags were used to log the activity of the participants, such as NFC tags placed on the doors of the 9 patient rooms to log when a participant entered or left a specific patient room. Other activities that were logged included the beginning and ending of meetings (medical rounds; daily, weekly, and monthly team meetings; and daily handovers at the beginning or end of a shift), the beginning and ending of conversations with patients or their relatives, and relaxation.

Furthermore, in addition to pressing the wristband button, as aforementioned, a stressful event could also be marked by scanning the NFC tags, which offered the possibility to communicate a challenging situation by entering a short description of the current event using a Huawei smartphone P30 lite. This smartphone, which hangs by a cord around the participants’ necks and can be stored conveniently in their gowns’ pockets with the microphone poking out (see Figure 2A), was also used to measure ambient noise.

Last, 2 types of interruptions were measured, each with a microphone attached to a Raspberry Pi 4 Model B. The first was an interruption by telephone calls (eg, outsiders calling to reach patients or to retrieve information about the patients such as family physicians or calls from within the hospital, eg, calling about referrals). The second kind of interruption was a distress call (from a patient) or an emergency call (from a fellow nurse or physician), both broadcast through the hospital ward’s bell system.

#### Questionnaires

Two types of questionnaires were used to assess subjective stress levels. An extensive study questionnaire with 137 items (101 of which ask for specific stressors) was handed out at the beginning of the study. It asked about the subjectively perceived frequency and participant’s rating of different stressors (ie, how often does this event take place and how stressful does one find it). A multiplication of the 2 parameters allowed for an evaluation of the perceived stress. Although an event could be labeled as very stressful, it was not necessarily a meaningful stressor if it rarely ever occurred. Thus, a stressful event that seldom took place or a frequent event that barely stressed the participant were both considered less harmful than an event that was both frequent and (moderately or highly) stressful. The study questionnaire was designed specifically for this study by a psychologist and a nurse with longstanding work experience, incorporating known stressors from the literature as well as stressors mentioned in a survey carried out in a palliative ward and an outpatient palliative care facility.

In addition, the Maslach Burnout Inventory [28] was handed out to assess further burdens (or possible sequelae of the stress). It is a standard questionnaire that will allow for interstudy comparisons of this study’s findings with those in the literature.

In addition to these 2 questionnaires that were only completed once at the beginning of the measurements, the subjective stress level was also assessed throughout the workday and accompanied the continuous ambulatory measurements using EMAs. EMAs are short questionnaires asking for self-reported information that documents the perceived subjective experience of stress at a certain moment (ie, a *momentary* appraisal of their *current* stress level) [29]. The questionnaires popped up on the participants’ smartphones whenever an NFC tag was scanned that indicated the end of an activity (eg, end of rounds, leaving a patient room, end of a meeting, end of speaking with a patient or his or her relatives) and asked, for example, “How stressed do you feel right now?” with a continuous slider from 0% to 100%, labeled in increments of 20%. In addition, the questionnaire could also be accessed at any time by scanning a designated NFC tag called “open questionnaire.” Additional EMAs popped up when the participant put the setup on at the beginning of a shift (greeting the participant, asking for the subjective sleep quality of the night before, and asking about his or her current stress level) and when the setup was removed and shut down at the end of the shift (asking for the current stress level, asking how many patients were looked after throughout the day, and wishing the participant a pleasant recreational time).

### Sample and Recruitment

The PCU at UMR, with its 14 beds, is the largest PCU in Mecklenburg-Western Pomerania, Germany. It employed 13 full-time nurses and 5 part-time nurses who work in a 3-shift system during the study implementation in 2021. Study participants had to be older than 18 years, their working time had to have a minimum of 20 hours per week, they had to have proficiency in written and spoken German, and they had to be employed at the palliative care unit at the Rostock University Medical Centre (inclusion criteria). Exclusion criteria comprised of nonconsenting capacity and nonfulfilment of all inclusion criteria. For the DiPa study, all 18 nurses working in the UMR PCU, who partly specialize in palliative care, were invited in December 2020 to participate in the study by presenting the procedure and aims of the project in a lecture as well as in a written inquiry. The measurement period for each participant was 6 weeks allowing for a total measurement duration of 3 months.

A power analysis was not conducted as the population was prespecified (N=18), rendering the need for an accruing sample. In the end, 12 nurses agreed to participate, resulting in a participation rate of 67% (12/18).

### Patient and Public Involvement

Patient involvement was not directly part of our study design because of the focus on nursing staff in palliative care. However, analogous to patients, our study participants were included in selected questions when we created the study design. As an example, preliminary tests could be used to compare measuring instruments with different measuring methods with regard to their wearing comfort and manageability. Furthermore, before starting the measurements, the nursing staff were shown a list of possible stressors in their work area. Anyone who had an additional suggestion could add it anonymously to this list. After the study design was developed further, the study was presented to the potential participants in an on-site presentation, as aforementioned. There was also the opportunity for questions and answers. Each nurse was free to take part in the study after having detailed knowledge of the study objective and carrying out the measurements on a daily basis.

Apart from our study participants, the public was not especially included in the planning phase. The expected results could affect the public and especially nurses in palliative care or other medical departments indirectly by identifying stress factors and their possible reduction.

### Procedures

After enrollment, each participant received thorough instruction on how to use the technical equipment. On the same day, each participant was interviewed separately to define their expectations and attitudes toward the DiPa study. Interviews were conducted by UMR staff who were not involved in the study (ie, a research assistant or a member of the central research center of the UMR). The answers were recorded during the interview and transcribed afterward to allow for an evaluation by independent raters to reduce bias and ensure data privacy. In addition, the participants completed the questionnaire on their perception of stressors and stress, including patient-associated stressors, working environment, team-associated stressors, and resources.

Participants were instructed to conduct the measurements during every shift. At the beginning of the shift, the participants gathered their equipment from their locker, put on the wristband, and picked up the smartphone. By turning on the wristband, a digital questionnaire appeared automatically on the smartphone’s display, welcoming the participant and asking for their current stress level as well as sleep quality of the previous night. Further free-text annotations were also possible. Participants then stored the smartphone in the pocket of their scrubs and began their workday.

Participants were instructed to use the smartphone to scan the corresponding NFC tag whenever entering a patient’s room. To this end, a green NFC tag with an arrow was placed on each patient room door. This event was thus recorded on the smartphone. Analogously, a red NFC tag was scanned when leaving the room. This not only recorded the event but also prompted a short questionnaire that was displayed on the smartphone’s screen, asked for their current stress level, and included a free-text space.

Special recurring processes on the PCU like daily visits, weekly and daily team meetings attended by nurses and physicians, and patient interviews had their own individual NFC tags denoting the start and end.

In parallel to data recording by the wristband and smartphone, the study team collected and analyzed data about the nurses (eg, how many worked in the ward per shift, length of work experience in years, and if they had the additional designation of “palliative care nurse,” as we expected an influence of workload for each participant). The second focus was patient-associated factors, especially the average, minimum, and maximum patient age and number of occupied beds per day. Because the PCU treats many critical ill patients with life-limiting diseases, we also thought it could be important to analyze the number of deaths per day.

